## Abstract

**Background:**

In breast cancer survivors, chemotherapy-induced muscle loss has been shown to be attenuated with structured resistance exercise. Creatine supplementation can increase bioenergetics in skeletal muscle, which helps to improve overall strength and endurance and reduce muscular fatigue. Therefore, we hypothesize that adding creatinine supplementation to exercise training will accelerate improvements in strength, endurance, and bioenergetics in breast cancer survivors.

**Objective:**

The primary objective is to determine the effects of combining creatine supplementation with exercise on modulating strength and physical function in breast cancer survivors by comparing these effects to those of exercise alone. The secondary objectives are to determine if creatine supplementation and exercise can increase the intramuscular storage of creatine and improve body composition by comparing this intervention to exercise alone.

**Methods:**

We aim to test our hypothesis by conducting an open-label randomized controlled trial of 30 breast cancer survivors who have completed chemotherapy within 6 months of enrollment. Eligible participants will be equally randomized (1:1) to either a creatine and exercise group or an exercise-only group for this 12-week intervention. Individuals who are randomized to receive creatine will be initially dosed at 20 g per day for 7 days to boost the availability of creatine systemically. Thereafter, the dose will be reduced to 5 g per day for maintenance throughout the duration of the 12-week protocol. All participants will engage in 3 center-based exercise sessions, which will involve completing 3 sets of 8 to 12 repetitions on chest press, leg press, seated row, shoulder press, leg extension, and leg curl machines. The primary outcomes will include changes in strength, body composition, and physical function in breast cancer survivors. The secondary outcomes will be intramuscular concentrations of creatine and adenosine triphosphate in the vastus lateralis, midthigh cross-sectional area, and quality of life.

**Results:**

As of October 2021, a total of 9 patients have been enrolled into the study. No unexpected adverse events have been reported.

**Conclusions:**

Creatine is being studied as a potential agent for improving strength, endurance, and bioenergetics in breast cancer survivors following chemotherapy. The findings from our trial may have future implications for supporting breast cancer survivors in reversing the muscle loss experienced during chemotherapy and improving their physical function and quality of life.

**Trial Registration:**

ClinicalTrials.gov NCT04207359; https://clinicaltrials.gov/ct2/show/NCT04207359

**International Registered Report Identifier (IRRID):**

PRR1-10.2196/26827

## Introduction

### Background

Survivorship after a breast cancer diagnosis is multifocal; it includes long-term care planning that is coordinated with a survivor’s oncologist, primacy care provider, and social work support and should include an active lifestyle that is inclusive of exercise. Yet, individuals with breast cancer are at high risk for skeletal muscle wasting, which may be exacerbated by cancer treatment or tumor-related factors [1,2] and can negatively impact the ability to complete activities of daily living. Lower extremity muscle weakness is also associated with long-term fatigue in breast cancer survivors [3]. Studies on resistance exercise interventions have reported notable improvements in strength, endurance, and body composition in breast cancer survivors [4,5]; however, identifying strategies for enhancing adaptations to exercise among cancer survivors is of importance.

In the context of cancer survivorship, a large percentage of cancer survivors exhibit a loss of muscle mass that impacts their ability to perform activities of daily living [6]. The root causes of this loss of muscle mass are cancer treatment and tumor proteins [6,7]. Muscle wasting in patients with cancer, in combination with normal aging processes, dramatically increases the risk of disability and accelerates the aging process [8]. Certain cancer therapies can exacerbate this decline in physical function and result in disabilities that patients cannot independently manage [9]. Resistance training has been demonstrated to improve physical function, muscular strength, and endurance in breast cancer survivors. However, the relationship among body mass, treatment toxicity, and cancer recurrence requires those in the field of exercise oncology to identify modalities for promoting such exercise adaptations. Therefore, we hypothesize that adding creatine supplementation to a structured resistance training intervention can lead to better improvements than those resulting from exercise alone.

Creatine is a naturally occurring substance in the human body that is synthesized endogenously in the kidneys, pancreas, and liver from amino acids (ie, arginine, glycine, and methionine) at a rate of approximately 1 to 2 g per day [10]. An additional 1 g per day of creatine is typically consumed through the diet of those who eat meat and fish [11]. In total, the creatine pool in skeletal muscle averages at about 120 g for a 70-kg individual with a proposed creatine capacity of up to 160 g (via supplementation) [12].

Approximately 2 g of creatine are lost per day through urination. However, aging is associated with an incremental loss of intramuscular creatine stores [13,14]. Notably, creatine supplementation has been shown to reverse this loss [15]. Studies have demonstrated the efficacy of creatine supplementation in augmenting training adaptations and have reported positive outcomes, such as improved strength and physical function in a variety of healthy and clinical populations [11,12]. Although some publications suggest that creatine supplementation alone can increase strength and work capacity and delay the onset of fatigue in older men and women [16-19], the majority of studies suggest that the benefit of creatine supplementation is greatest when it is combined with hypertrophic stimuli, such as resistance exercise training [20].

Creatine supplementation has gained attention in the medical field because of the numerous health and quality of life benefits it has for people with muscular and neurological diseases, such as McArdle disease, Duchene dystrophy, myasthenia gravis, amyotrophic lateral sclerosis, and Parkinson disease, and its limited side effects [21]. Creatine is crucial to maintaining muscle energetics because of its role in rephosphorylating adenosine diphosphate to adenosine triphosphate (ATP). To date, few studies have examined the use of creatine supplementation to augment cancer treatment–associated declines in muscle mass and function [22-25]. Those that exist have generally failed to demonstrate its benefits for strength and function. A limitation to these studies is that most have investigated creatine supplementation alone. Only 1 study of cancer survivors has been published on combining creatine supplementation with resistance training, which resulted in improvements in lean body mass [22]. No such studies to date have been conducted on patients with breast cancer—a population that is particularly vulnerable to the loss of lean mass and function. Despite the benefits of exercise on reversing the anthracycline-related effects on muscle wasting, breast cancer survivors remain fatigued and deconditioned long into survivorship [26]. Therefore, there is a significant need to identify alternative strategies for reversing the known deleterious effects of chemotherapy in this population. The paucity of research in this area stems from the lack of awareness of the potential role that creatine supplementation plays in cancer survivors.

### Safety and Toxicity of Creatine

Creatine has not been evaluated by the Food and Drug Administration for safety; however, it is a widely used over-the-counter supplement. Creatine is one of the most highly studied supplements, and numerous studies have demonstrated its safety and tolerability [12,27]. In the four papers published to date on creatine supplementation in patients with cancer [22-25], only 2 of the 333 patients who were taking creatine reported any adverse effects (muscle cramping and mucus production) [22]. Other commonly identified side effects of creatine supplementation include nausea, diarrhea, dizziness, and gastrointestinal pain, but their severity is often mild [12,27].

### Study Objectives

The primary objective is to determine the effects of creatine supplementation, in combination with exercise, on modulating strength, body composition, and physical function in breast cancer survivors by comparing these effects to those of exercise alone. The primary hypothesis is that creatine supplementation will result in significantly greater gains in strength and physical function and improved body composition in breast cancer survivors compared to those resulting from exercise alone.

The secondary objectives are to determine if supplemental creatine can be used to increase intramuscular storages of creatine, alter energy storage, and improve quality of life. The hypothesis for these objectives is that creatine supplementation will significantly increase intramuscular concentrations of creatine and ATP in the vastus lateralis when compared to exercise-only controls. We also hypothesize that the creatine group will have significantly greater muscle cross-sectional areas and significantly lower levels of intramuscular fat compared to those of the exercise-only controls. Finally, we hypothesize that both groups will have a significantly better quality of life following the 12-week program.

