### Study Population

The study will enroll 30 patients with breast cancer who have completed chemotherapy within 6 months prior to consenting to this study. The recruitment methods include media advertisements, community events, and queries of institutional medical records for potentially eligible subjects. The inclusion criteria are the following: (1) an age of 18 to 75 years; (2) a diagnosis of breast cancer and the recent (within 6 months) completion of chemotherapy; (3) the willingness to attend 3 exercise sessions per week; (4) the ability to take oral medications; (5) the willingness and ability to provide consent for participating in the study; and (6) a serum creatinine level of ≤1.5 times the upper limit of normal or an estimated glomerular filtration rate of ≥30 mL/min/1.73 m^2^, as determined by the Chronic Kidney Disease Epidemiology Collaboration equation. The exclusion criteria are as follows: (1) physical indications that performing exercise may be limited or contraindicated; (2) poorly controlled hypertension (resting systolic blood pressure: >160 mm Hg; resting diastolic blood pressure: >95 mm Hg); (3) current tobacco use (within 6 months); (4) anabolic steroid use; (5) a pitting edema grade of 2+; (6) patients who are currently undergoing medical treatment for cancer (ie, currently undergoing chemotherapy; radiation therapy is allowed); (7) a history of moderate-severe heart disease (New York Heart Classification of >grade II) or pulmonary disease (dyspnea on exertion upon climbing ≤1 flight of stairs and abnormal breath sounds on auscultation); (8) pregnant patients or patients who are planning to become pregnant during the study; (9) recent (within 1 month) or anticipated treatment with corticosteroids (except those for short-term use during the time of chemotherapy) or other appetite stimulants; (10) bipolar disorder; (11) creatine supplementation within the past 30 days; and (12) a change in supplement use within the past 14 days.

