#### Outcome Assessments

Assessments will be performed at baseline and at the end of the study (Table 2).

**Table 2 table2:** Study assessments and methods.

Assessment	Method
Renal function testing, metabolic panels, and lipid and complete blood count tests	Lab test
Muscle strength (power and torque)	Dynamometry
Muscle strength	1-repetition maximum and 10-repetition maximum training
Body composition and bone density	Dual x-ray absorptiometry
Muscle cross-sectional area	Magnetic resonance imaging
Muscle creatine, phosphocreatine, and adenosine triphosphate	Magnetic resonance spectroscopy
Physical function	6-minute walk test
Quality of life	European Organization for Research and Treatment of Cancer Quality of Life Questionnaire-C30 and European Organization for Research and Treatment of Cancer Quality of Life Questionnaire-BR23

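### The quality-of-life hypothesis predicts that both groups improve, so confirming it would not answer the stated objective of whether creatine improves quality of life

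*Protocol article*

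**What the plan says.** Study Objectives in the protocol article lists, among the secondary aims, to "determine if supplemental creatine can be used to increase intramuscular storages of creatine, alter energy storage, and improve quality of life". The quality-of-life hypothesis then reads: "Finally, we hypothesize that both groups will have a significantly better quality of life following the 12-week program".

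The two other secondary hypotheses in that section name the control arm. One is that "creatine supplementation will significantly increase intramuscular concentrations of creatine and ATP in the vastus lateralis when compared to exercise-only controls". The other, on muscle area and fat, ends with "significantly lower levels of intramuscular fat compared to those of the exercise-only controls". The primary hypothesis is likewise framed against exercise alone.

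Quality of life is a listed secondary outcome (abstract, Methods: "The secondary outcomes will be intramuscular concentrations of creatine and adenosine triphosphate in the vastus lateralis, midthigh cross-sectional area, and quality of life"). On timing, Outcome Assessments says: "Assessments will be performed at baseline and at the end of the study". The instruments are the EORTC QLQ-C30 and QLQ-BR23, completed by the participants. Statistical Analysis mentions quality of life only in a Pearson correlation analysis with body composition and physical function.

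**The concern.** Creatine is the only planned difference between the arms, so a question about what creatine does to quality of life is a between-arm question. A prediction that both arms will be better afterwards is about change over time, and it can come true whether or not creatine does anything.

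There are several reasons to expect improvement in both arms here. Eligibility requires "a diagnosis of breast cancer and the recent (within 6 months) completion of chemotherapy", so some recovery over 12 weeks is plausible. Everyone trains three times a week. Participants are not blinded and report the outcome themselves. With no arm that does not exercise, improvement in both groups could not be credited cleanly to the exercise programme either.

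The risk is that the trial reports its quality-of-life hypothesis as confirmed and readers take this as an answer to the creatine objective.

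**Working it through.** **Setting the statements side by side (Study Objectives)**

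| Item | Comparator stated |
|---|---|
| Strength, function, body composition (primary hypothesis) | Exercise alone |
| Intramuscular creatine and ATP | Exercise-only controls |
| Muscle area and intramuscular fat | Exercise-only controls |
| Quality of life | None; both groups predicted to improve |

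Nothing in Statistical Analysis supplies the missing comparison. The correlation analysis is not a treatment contrast, and the log-rank and Cox analysis given as primary is not linked to quality of life.

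**Illustration of size.** The article states no power, SD or effect size for quality of life, so there is no figure of its own to reproduce.

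Inputs from the article:
- 15 enrolled per arm, with a goal of 12 completers per arm (Allocation).
- Two-sided significance level of 0.05 (Statistical Analysis).

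Assumptions:
- No creatine effect.
- The same mean improvement in both arms, d, in SDs of the change score.
- Independent arms, and a paired t test within each. The test is my reading of what significant improvement in both groups would entail; the article names none.

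Chance that one arm shows a significant improvement, from the noncentral t distribution:

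p = 1 − F(t₀.₉₇₅,ₙ₋₁ ; df = n − 1, noncentrality = d√n)

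For n = 12 the noncentrality is 0.5 × √12 = 1.73 or 0.8 × √12 = 2.77. The hypothesis needs both arms, so its chance of confirmation is p². The chance that exactly one arm is significant is 2p(1 − p).

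| n per arm | d | One given arm, p | Both arms, p² | Exactly one arm |
|---|---|---|---|---|
| 12 | 0.3 | 0.156 | 0.024 | 0.264 |
| 12 | 0.5 | 0.353 | 0.124 | 0.457 |
| 12 | 0.8 | 0.714 | 0.509 | 0.409 |
| 12 | 1.0 | 0.883 | 0.779 | 0.207 |
| 15 | 0.3 | 0.190 | 0.036 | 0.308 |
| 15 | 0.5 | 0.438 | 0.192 | 0.492 |
| 15 | 0.8 | 0.821 | 0.675 | 0.294 |
| 15 | 1.0 | 0.949 | 0.901 | 0.097 |

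A between-arm test would reject in 5% of such trials at every d, provided that knowing the allocation does not itself shift the answers.

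**What a between-arm comparison could detect.** For an unadjusted two-sample t test with 80% power, the detectable difference in mean change is 1.20 SD at 12 per arm and 1.06 SD at 15 per arm. The normal approximation gives (1.960 + 0.842) × √(2/12) = 1.14 and (1.960 + 0.842) × √(2/15) = 1.02.

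**The case against.** The hypothesis is an expectation, not an analysis. A reader might infer that the plan prescribes an uncontrolled paired test and throws away the randomized comparison. The article does not support that: it names no within-arm quality-of-life test, the outcome is collected in both randomized arms at both time points, and an analysis plan not shown here could specify the contrast. This part of the objection stands, and it limits the point to a mismatch between objective and hypothesis. It does not remove the mismatch, which lies in the text.

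A reader might also take the single-arm probabilities (35% and 71% at 12 per arm) as the chance of misleading success. They are not, because the hypothesis requires both arms.

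Nor are the joint figures false positives for the hypothesis as worded. If both arms truly improve, saying so is correct. The error arises only when the result is used to answer the creatine objective. Reading an effect from significance in one arm only would also be invalid, but the article does not propose doing so.

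Finally, randomization does not protect a self-reported outcome from expectation in an open-label trial without placebo. That is correct: the between-arm contrast removes recovery and exercise effects common to both arms, but not differential expectation. Quality of life is also secondary in a trial of 30 sized for feasibility, and no decision rule rests on it.

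**Conclusion.** The point holds as a mismatch. The objective asks what creatine does, while the hypothesis predicts improvement in both groups and alone in its section names no comparator. Confirming it would say nothing about creatine. With no creatine effect and an assumed common drift of 0.5 or 0.8 SD of the change score, both arms would be significant in about 12% or 51% of trials at 12 per arm, and 19% or 68% at 15 per arm. At 0.3 SD the figure is only 2% to 4%, so the size depends heavily on the drift assumed. It also rests on independent arms and on within-arm paired tests, which are inferred from the wording. The defect is in the hypothesis, not in the design or the data collected. It should be corrected, but its weight is moderate.

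**What to change.** Restate the quality-of-life hypothesis as a difference between groups at 12 weeks, adjusted for the baseline value of the same score and reported with a 95% CI. The EORTC QLQ-C30 global score is one suitable choice; the article does not dictate it. Keep within-group changes as description, and say that they are not attributed to creatine.

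The change is one of wording: same questionnaires, visits and sample size. Three costs should be stated openly:
- The claim that both groups improved significantly is given up as a hypothesis.
- The between-group estimate will be imprecise: 80% power only for about 1.2 SD at 12 per arm without adjustment, though baseline adjustment may lower this somewhat. The interval is the useful result, which fits a trial meant to inform later sample sizes.
- Open-label self-report can still bias the contrast, so that limitation belongs beside the result.

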### Trial Design

Our prospective study is a single-center, open-label randomized controlled trial. Figure 1 shows the study design, and Table 1 presents the schedule of events. This study protocol follows the SPIRIT (Standard Protocol Items: Recommendations for Interventional Trials) Statement recommendations [28].

**Figure 1 figure1:**
[figure not shown]
Individuals randomized to the creatine group will exercise 3 times per week for 12 weeks and take creatine in powder form as indicated. Individuals in the control group will exercise 3 times per week for 12 weeks without creatine dosing.

**Table 1 table1:** Study schedule of events.

Event	Screen day (−28 to −7 days)	Baseline assessments (−7 to −2 days)			Study week				12-week end-of-study assessments (>2 days and <7 days after the last exercise session)	
		Visit A	Visit B	Week 2		Week 5	Week 9	Visit A		Visit B
Phone screen	✓									
Physical exam	✓							✓		
Medical history	✓			✓		✓	✓	✓		
Medication history	✓			✓		✓	✓	✓		
Clinical labs	✓			✓				✓		
Electrocardiography	✓			✓						✓
Vital signs	✓							✓		
Height	✓									
Weight	✓							✓		
Body circumference	✓							✓		
Waist to hip ratio	✓							✓		
Mood disorder questionnaire										
Pregnancy test		✓						✓		
Handgrip dynamometry		✓						✓		
Isometric leg strength		✓						✓		
Dual x-ray absorptiometry		✓						✓		
6-minute walk test		✓						✓		
Survey completion		✓						✓		
Magnetic resonance imaging and magnetic resonance spectroscopy			✓							✓
1-repetition and 10-repetition maximum testing			✓							✓
Exercise familiarization			✓							
Dispense creatine (20 g/day)			✓							
Dispense Creatine (5 g/day)				✓		✓	✓			

## Methods

### Ethical Approval

This trial has been approved by the institutional review board at the University of Texas Health Science Center at San Antonio and the protocol review committee at the National Cancer Center Institute Mays Cancer Center at the University of Texas Health Science Center at San Antonio (2019-610H). All participants who meet the inclusion criteria will be eligible for participation. Any deviations from the protocol, breaches of confidentiality, and reportable adverse events will be reported to the institutional review board and Data Safety Monitoring Board at the Mays Cancer Center. The study is registered with ClinicalTrials.gov (trial number: NCT04207359).

### Study Setting

The study will enroll breast cancer survivors from San Antonio, Texas, and the surrounding community. The majority of the patients who will be enrolled in this study will be patients of the Mays Cancer Center at the University of Texas Health Science Center at San Antonio—a National Cancer Institute–designated cancer center. An interprofessional team of exercise physiologists, medical oncologists, nutritionists, mental health professionals, personal trainers, research coordinators, and research assistants will implement the various aspects of this study.

### Study Population

The study will enroll 30 patients with breast cancer who have completed chemotherapy within 6 months prior to consenting to this study. The recruitment methods include media advertisements, community events, and queries of institutional medical records for potentially eligible subjects. The inclusion criteria are the following: (1) an age of 18 to 75 years; (2) a diagnosis of breast cancer and the recent (within 6 months) completion of chemotherapy; (3) the willingness to attend 3 exercise sessions per week; (4) the ability to take oral medications; (5) the willingness and ability to provide consent for participating in the study; and (6) a serum creatinine level of ≤1.5 times the upper limit of normal or an estimated glomerular filtration rate of ≥30 mL/min/1.73 m^2^, as determined by the Chronic Kidney Disease Epidemiology Collaboration equation. The exclusion criteria are as follows: (1) physical indications that performing exercise may be limited or contraindicated; (2) poorly controlled hypertension (resting systolic blood pressure: >160 mm Hg; resting diastolic blood pressure: >95 mm Hg); (3) current tobacco use (within 6 months); (4) anabolic steroid use; (5) a pitting edema grade of 2+; (6) patients who are currently undergoing medical treatment for cancer (ie, currently undergoing chemotherapy; radiation therapy is allowed); (7) a history of moderate-severe heart disease (New York Heart Classification of >grade II) or pulmonary disease (dyspnea on exertion upon climbing ≤1 flight of stairs and abnormal breath sounds on auscultation); (8) pregnant patients or patients who are planning to become pregnant during the study; (9) recent (within 1 month) or anticipated treatment with corticosteroids (except those for short-term use during the time of chemotherapy) or other appetite stimulants; (10) bipolar disorder; (11) creatine supplementation within the past 30 days; and (12) a change in supplement use within the past 14 days.

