### Creatine Dosing Protocol

Participants who are randomized to receive creatine (experimental group) will be initially dosed at 20 g per day for 7 days to boost the availability of creatine systemically [32]. Thereafter, the dose will be reduced to 5 g per day for maintenance throughout the duration of the 12-week protocol. This dosing protocol is based on the traditional dosing protocol for healthy individuals, which includes a loading phase (5 g of creatine taken 4 times per day) that is followed by a low-dose maintenance period (5 g of creatine per day) for maintaining creatine stores [12]. The individuals in this group will receive creatine in powder form at 4 different schedules based on their progress throughout the protocol. Each bottle of creatine will contain a 5-mg dosing spoon. Bottle 1 will be provided at the start of the study, and an equivalent dose for the loading phase will be assigned in week 1 of the study. In week 2, participants will return to the clinic and be provided with 21 days’ worth of creatine doses (5 g/day). At weeks 5 and 9, participants will again return to the clinic and be given 28 days’ worth of creatine doses (5 g/day). Bottles will be exchanged at these scheduled intervals, and dosing adherence will be determined by measuring the amount of creatine that remains in the bottles. For weeks 2 to 12, participants will also be asked to take the creatine at approximately the same time of the day and enter the time of dosing in a dosing diary. The individuals in this group will have safety labs drawn after the loading phase to ensure normal kidney function, and electrocardiography will be performed to rule out any abnormalities. Participants will be removed from the creatine group if the lab results show serum creatinine levels of >2 times the upper limit of normal or estimated glomerular filtration rates of <30 mL/min/1.73 m^2^. These participants will complete the remaining exercise interventions.

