#### Screening Visit

At the screening visit, participants will read and sign the informed consent form. Once consent is provided, a complete medical history and physical exam will be performed to ensure that the participants meet the inclusion criteria for the study. This will include measurements of vital signs, height, and body weight. Blood will be collected following an overnight fast for clinical lab tests, which will include renal function testing, comprehensive metabolic panels, and lipid and complete blood count tests. Resting electrocardiograms will be acquired and evaluated by a clinician to confirm a healthy heart rate and rhythm. Questions regarding the intent to become pregnant will be asked. A mood disorder questionnaire will be completed by participants and evaluated by study staff to assess for bipolar mood disorder. Subjects who meet the study eligibility criteria will be scheduled for study assessments.

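### The renal entry criterion and the creatine removal rule overlap: as worded, a participant can be eligible for the loading dose with a screening value already past the removal limit

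*Protocol article*

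**What the plan says.** **Entry.** Study Population, inclusion criterion 6, requires "a serum creatinine level of ≤1.5 times the upper limit of normal or an estimated glomerular filtration rate of ≥30 mL/min/1.73" m², with eGFR "as determined by the Chronic Kidney Disease Epidemiology Collaboration equation". None of the 12 exclusion criteria in that section sets a renal limit. The Ethical Approval section states that meeting the inclusion criteria makes a participant eligible.

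**Screening.** Under Screening Visit: "Blood will be collected following an overnight fast for clinical lab tests, which will include renal function testing". The same section continues: "Subjects who meet the study eligibility criteria will be scheduled for study assessments".

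**Removal.** The Creatine Dosing Protocol section stops creatine for "serum creatinine levels of >2 times the upper limit of normal or estimated glomerular filtration rates of <30 mL/min/1.73" m². People removed on this rule finish the exercise programme. The timing of the labs is given just before: "The individuals in this group will have safety labs drawn after the loading phase to ensure normal kidney function".

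**Schedule.** Table 1 places clinical labs at screening, at week 2 and at the end of study. The 20 g/day supply is dispensed at baseline Visit B, between the first two.

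**The concern.** Entry is satisfied when either of two renal limits is passed. Removal is triggered when either of two renal limits is failed. Rules built this way are not complements of each other, so some values satisfy both. A participant with such values could enter, be randomised to creatine and take the highest dose in the protocol (20 g/day for 7 days) at a renal value that the same protocol treats as a reason to stop creatine.

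What is at stake is participant safety and the coherence of two safety rules. Only the creatine arm is exposed, which is a planned 15 of 30.

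**Working it through.** **Step 1: the logic, from the protocol alone.** Write C for creatinine as a multiple of ULN and G for eGFR in mL/min/1.73 m².

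- Eligible on renal grounds: C ≤ 1.5 or G ≥ 30.
- Removed from creatine: C > 2 or G < 30.

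| C | G | Eligible as written | Removal limit met | Eligible if 'and' |
|---|---|---|---|---|
| 1.4 | 35 | yes | no | yes |
| 1.4 | 25 | **yes** | **yes** | no |
| 1.7 | 35 | yes | no | no |
| 1.7 | 25 | no | yes | no |
| 2.1 | 35 | **yes** | **yes** | no |
| 2.1 | 25 | no | yes | no |

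The two overlap regions are:

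- A: C ≤ 1.5 with G < 30.
- B: C > 2 with G ≥ 30.

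Reading the eGFR limit as a fallback, consulted only when creatinine exceeds 1.5 × ULN, does not help. Region A is still admitted on creatinine, and region B is still admitted on the fallback.

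**Step 2: is the overlap reachable?** This needs figures the protocol does not give, so these are assumptions: CKD-EPI in its 2009 and 2021 forms, creatinine reported to 0.01 mg/dL, and a ULN of 0.9 to 1.3 mg/dL for women. Ages 18 to 75 come from the protocol. For women with creatinine S above 0.7 mg/dL:

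- 2009: eGFR = 141 × (S/0.7)^−1.209 × 0.993^age × 1.018
- 2021: eGFR = 142 × (S/0.7)^−1.200 × 0.9938^age × 1.012

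Example for region B: ULN 1.0, age 30, S = 2.05, so C = 2.05. The 2021 form gives 142 × (2.929)^−1.200 × 0.9938^30 × 1.012 = 32.8; the 2009 form gives 31.7. Eligible, and past the creatinine removal limit.

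Example for region A: ULN 1.2, age 75, S = 1.80, so C = 1.5. The 2021 form gives 142 × (2.571)^−1.200 × 0.9938^75 × 1.012 = 29.0; the 2009 form gives 27.1. Eligible, and past the eGFR removal limit.

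Ages at which women can fall in the overlap (2009 / 2021):

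| Assumed ULN, mg/dL | Region A | Region B |
|---|---|---|
| 0.9 | none | 18–59 / 18–68 |
| 1.0 | none | 18–41 / 18–48 |
| 1.1 | none | 18–24 / 18–30 |
| 1.2 | 61–75 / 70–75 | none |
| 1.3 | 47–75 / 55–75 | none |

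The windows are narrow. At ULN 1.0 the widest is at age 18, creatinine 2.01–2.30 / 2.01–2.35. At ULN 1.2 the widest is 1.66–1.80 / 1.76–1.80. Women aged 49 to 60 have no overlap at ULN 1.0, 1.1 or 1.2 under either form.

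**Step 3: the candidate repairs.**

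- 'And' in criterion 6 (C ≤ 1.5 and G ≥ 30): nobody eligible can have C > 2 or G < 30, so the overlap is empty.
- Criterion 6 kept, plus an exclusion for C > 2 or G < 30: (C ≤ 1.5 or G ≥ 30) and C ≤ 2 and G ≥ 30. Once G ≥ 30 is required, the bracket is always true, so this reduces to G ≥ 30 and C ≤ 2. The overlap is again empty, but the present criterion 6 no longer does any work.

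**The case against.** The strongest reply is that no participant need ever be affected. Medical history, physical examination and renal tests all precede scheduling, medical oncologists are on the team, and a clinician who saw an eGFR below 30 would be likely to act. The article condenses a fuller protocol that may say how abnormal screening results are handled. Labs after the loading week would pick up a value that was still past a limit.

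Much of this stands. A reader might infer that abnormal screening results will be ignored, or that someone will be loaded at an unsafe value. The document supports neither: it shows only that no written rule requires action before loading. Silence on how abnormal labs are handled is not itself a fault in an article.

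It is also fair that reachability rests on an assumed ULN and an unstated version of the equation, and that for many ages and ULNs the overlap is empty.

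What the reply does not remove is the conflict in the printed text. Both rules carry explicit thresholds, and followed exactly they allow entry at a value that requires stopping. Post-loading labs limit the exposure to about a week, but they come after the 20 g/day phase.

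**Conclusion.** The inconsistency is real on the wording, and that conclusion needs no outside figure. It is of the lowest severity, worth considering. Its practical size cannot be estimated from the document: which of the two profiles can occur depends on the ULN, the creatinine windows are narrow under the assumptions used, and the number affected among 30 may be zero. A reader might take it as a threat to the trial's comparisons; nothing in the protocol supports that, because no outcome or analysis uses these limits.

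**What to change.** Change 'or' to 'and' in inclusion criterion 6: creatinine ≤1.5 × ULN and eGFR ≥30 mL/min/1.73 m². This empties the overlap and keeps a creatinine margin between entry (1.5 × ULN) and removal (2 × ULN). It uses screening labs already drawn. The cost is an occasional extra screen failure, including people with creatinine above 1.5 and up to 2 × ULN and eGFR ≥30, whom the removal rule would let continue. For a woman aged 50 at an assumed ULN of 1.0 mg/dL, that bars creatinine 1.51–1.91 (2009 form, eGFR 39.9–30.0) or 1.51–1.99 (2021 form, eGFR 41.9–30.1).

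If the sponsor wants to keep those people, there are two alternatives:

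- Replace criterion 6 with eGFR ≥30 and creatinine ≤2 × ULN. This equals adding an exclusion at the removal limits, so the present criterion should be deleted and not left in place. It bars only people already past a removal limit, but leaves no margin on either measure before loading.
- Leave entry alone and require that screening labs not meet the removal limits before the loading supply is dispensed at baseline Visit B.

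Each is a one-line change.
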